**Fig 4 pone.0279021.g004:**
[figure not shown]
Example of a single trial.

The task was computed using PsychToolBox-3 (http://psychtoolbox.org/) in Matlab and will be presented on a desktop computer.

## 8. Randomization

Participants are not randomized (within-subjects design), however, the trials that participants will complete are quasi-random. That is to say, trials will appear in a random order, which ensures a balanced design and equal probabilities of each trial occurring.

Sampling Plan

## 9. Existing data

Registration prior to the creation of data. Ethical Approval was obtained on June 2. 2022 (projet 2022–521 Université Fédérale Toulouse Midi-Pyrénées)

## 10. Data collection procedures

Recruitment:

*Recruitment method*: the participants are recruited by e-mail and via paper announcements in the institute buildings.

*Place of recruitment*: participants will be recruited at ISAE-SUPAERO

*Selection criteria*: Subjects must be between 18 and 30 years old, have a level of study baccalaureate minimum, have a normal or corrected-to-normal vision and hearing, be affiliated with social security and have signed an informed consent form.

*Exclusion criteria*: Protected persons, a person outside the ISAE, presence of known neuropsychological disorder, significant visual or hearing impairment, taking psychotropic medication or substance, g-test positive, nursing woman. In addition, due to the nature of the experiment, colorblind people will be excluded from participation.

As recommended to minimize the risk of an invasion of privacy, we will list all the criteria (inclusion and/or exclusion) and ask participants whether they meet all the criteria, rather than asking them whether they meet each criterion one by one. Due to the nature of the experiment, participants will also complete a test for colorblindness prior to signing the inclusion/exclusion criteria. To do so we will use the Ishihara test for colorblindness (Hardy et al., 1945), which is widely applied and validated within science and medicine.

Compensation for subjects:

Participants will be paid in gift vouchers (Illicado, illicado.com). Upon completion participants will receive a voucher worth 20€ (5€ for the first training session, and 15€ (for the longer testing session). Should participants drop out after the first session they will be informed that they have the right to receive the 5€ voucher nevertheless.

**Protocol:** In the experiment participants will complete the DTS protocol as presented above.

After the arrival of the participant for the first session, the participant will be asked to complete the Ishihara colorblindness test, before filling in the informed consent and information sheets. The participant will be informed, that they are permitted to ask questions at any time, and are also asked in what language they would like to perform the task (French or English). They will then fill in the Demographics questionnaire, the Edinburgh Handedness questionnaire and a KSS as well as the SPS scale. Next, the participant will be familiarized with the DTS protocol, and perform a training session, until the participants have acquired an adequate level of skill in the task.

For the training session, participants will perform at least 5 blocks (96 trials each, 3,5 min without feedback, 4 minutes with feedback) of the DTS protocol. During the first block, participants will receive feedback following each trial, to increase their individual learning rates. Subsequent blocks will exclude the feedback to completely mimic the experimental conditions. Additional blocks of training may be added following the 5 blocks to ensure adequate task performance. Additional training may be added, if the last completed block of trials, still shows a significant improvement over the preceding trial. Additional blocks will only be added with the explicit consent of the participant.

After the training session, the participant will again fill in a KSS as well as an SPS scale.

The second session will be scheduled no longer than 14 days after the first session. The procedure of the second session is largely similar to that of the first session. Participants will perform a much shorter second training session intended to help the participant remember the task. Participants will complete half a block of trials (48 trials) with feedback and another half block without feedback. Next participants will fill in a KSS and SPS scale and perform the experimental DTS protocol as detailed above. Participants will complete 5 Blocks of 336 trials each. In between blocks participants will have a short break of 28 seconds as proposed by Lim et al., 2016, to avoid recovery from the TOT effects.

Upon completion of the task participants will again fill in the KSS and SPS scale, before being thanked for their participation and paid (See Fig 5).

**Fig 5 pone.0279021.g005:**
[figure not shown]
Timeline of the two sessions for Experiments 1 and 2.

## 11. Sample size (required)

The approximate range of required participants was determined using G*Power [37] Based on the reported statistics [3,15]. Their reported effect sizes ranged from 0.84 to 1.81 (f-squared). For a one-tailed test with an alpha of 0.05. The sample size required ranges from 15–25 participants. These numbers are only approximations, as the effects that we intend to observe are not exactly the same as the ones reported in the aforementioned studies. We intend to collect data from 30 participants, in order to assure an adequate effect size.

Variables

## 12. Manipulated variables (optional)

Stimuli:

**Numeric Value:** The value of the stimuli that are presented is manipulated. Participants with see combinations of the numbers 1,2,3,4,6,7,8 and 9 and symbols %, &, € and $.

**Color:** The stimuli color is manipulated to either be hot (red/orange hues), cold (blue/ green hues) or neutral (grey hues).

**Pattern:** The pattern of the stimuli is manipulated and can either show a horizontally oriented pattern, a vertically oriented pattern or a random pattern.

**Task:** The task that participants have to complete given the stimuli can be adapted as can be seen in Figs 1 and 2 the four tasks are Low/High, Even/Odd, Cold/Hot, Vertical/Horizontal.

**Conflict**: Depending on what stimuli are presented together the experiment manipulates the degree of conflict. See Fig 3.

**Conflict Congruency:** The conflict stimuli can be either congruent or incongruent with the task relevant stimulus.

Covariate:

Time on task (TOT), how long the participant has been performing the task, will be incorporated into the analysis as a key covariate indicator of mental fatigue.

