## 2. Hypotheses (required)

2.1. Task switching cost
2.1.1. Following a switch of the task, the reaction time on said trial is higher than the average reaction time on trials of the same task where previously no switch occurred.2.1.2. Following a switch of the task, accuracy on said trial is lower than the average accuracy on trials of the same task where previously no switch occurred.2.2. Similarity Effects: Task Switching costs (hypothesis 1; Reaction time and accuracy), are more pronounced if the switch is between two more dissimilar tasks.2.3. Conflict Effects:
2.3.1. An incongruent stimulus will result in a higher reaction time regardless of whether the trial is a switch trial or a repetition trial.2.3.2. An incongruent stimulus will result in a lower accuracy regardless of whether the trial is a switch trial or a repetition trial.2.4. Mental Fatigue:
2.4.1. As time on task increases, the reaction times will increase regardless of whether the trials are switch trials or repetition trials.2.4.2. As time on task increases, error likelihood will increase regardless of whether the trials are switch trials or repetition trials.2.4.3. As time on task increases, Task Switching costs (hypothesis 1) will increase

Design Plan

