### KSS

The KSS was developed to measure subjective sleepiness at any given time. It is a simple 9-point scale ranging from “extremely 1 = alert” to “9 = extremely sleepy–fighting sleep”. The scale has been validated and used frequently and provides a simple and fast measure that at the same time provides a reliable result [39]. The scale is attached in Appendix 7 in S1 Appendix.

SPS:

SPF: The estimation of fatigue will be performed using the Samn-Perelli Fatigue scale (SPF; [40]). This scale consists of 7 points and is used in aviation to assess crew fatigue. The French version comes from a report by the International Civil Aviation Organization [41]), but has not been psychometrically validated (see Appendix 6 in S1 Appendix).

Ishihara Colorblindness Test:

The Ishihara test for colorblindness [41] encompasses stimuli, that can determine the degree as well as the type of colorblindness, a person has. It will be presented in printed form, using a validated version of the test made available by the US department of infectious diseases (see Appendix 9 in S1 Appendix). Participants will be informed, that for a medically accurate test, a licensed physician is required. Should the suspicion of colorblindness arise during the assessment participants will be informed and advised to seek out a medical professional.

**The St Mary’s Hospital Sleep Questionnaire** (QSN; [42]) will be used to estimate the quality of sleep on the previous night. A translated version of this questionnaire has been produced (see Appendix 10 in S1 Appendix). The scoring of this questionnaire is not standardized due to the use of Likert scales and free responses. In addition, two questions regarding caffeine consumption have been added to this questionnaire.

Analysis Plan

The Analysis will be performed using Mixed (Multi-Level) Regression, as this allows for accounting for the effects of participants as well as tasks.

A first mixed multilevel regression will be performed on the dependent variable of RT (in MS).

The **independent Variables** are Trialtype (3 Levels), Conflict (4 Levels), Conflict Congruency (Binary) and Response (Binary)

The **dependent variable** is RT (in MS).

Time on Task (Time since task onset) will be included as a **covariate**

In a second Mixed multilevel logistic regression accuracy will be analyzed.

The **independent Variables** are Trialtype (3 Levels) and Conflict (4 Levels) and Conflict Congruency (Binary)

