The **dependent variable** is Accuracy (Binary)

Time on Task (Time since task onset, and or trial number) will be included as a **covariate**

In order to account for both participants as well as task effects, both will be dummy coded and included as IV effects in the Mixed Regression for both analyses. In order to best determine the most fitting covariance structure, the analysis will first be performed with a random intercept + ARMA (or AR1). Random slopes may be added if the fixed model is reduced or following a test for slope variance of the IV effects.

Expected Results: The expected results based on the hypotheses are detailed in Table 1.

**Table 1 pone.0279021.t001:** Expected results with corresponding hypotheses.

	Hypothesis	Expected effect
Task-Switching Costs	Following a switch of the task, reaction time on said trial is higher than the average reaction time on trials of the same task where previously no switch occurred	The effect of trial-type (switch vs repeat) is significant in the Mixed Multilevel Regression (higher RT for switches)
	Following a switch of the task, accuracy on said trial is lower than the average accuracy on trials of the same task where previously no switch occurred.	The effect of trial-type (switch vs repeat) is significant in the Mixed Multilevel Logistic Regression (lower accuracy for switches)
Similarity effects	For all switch trials, reaction time will be longer if the switch occurs between dissimilar tasks	The interaction effect between trial-type (switch vs repeat) and similarity is significant in the Mixed Multilevel Regression (higher RT for dissimilar switches)
	For all switch trials, accuracy will be lower if the switch occurs between dissimilar tasks	The interaction effect between trial-type (switch vs repeat) and similarity is significant in the Mixed Multilevel Logistic Regression (lower accuracy for dissimilar switches)
Conflict effects	An incongruent stimulus will result in a higher reaction time regardless of whether the trial is a switch trial or a repetition trial.	The effect of congruency (congruent vs incongruent) is significant in the Mixed Multilevel Regression (higher RT for incongruent trials)
	An incongruent stimulus will result in a lower accuracy regardless of whether the trial is a switch trial or a repetition trial.	The effect of trial-type (congruent vs incongruent) is significant in the Mixed Multilevel Logistic Regression (lower accuracy for incongruent trials)

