Mental fatigue	As time on task increases, the reaction times will increase regardless of whether the trials are switch trials or repetition trials.	The covariate of TOT is significant in the Mixed Multilevel Regression (higher RT over time)
	As time on task increases, error likelihood will increase regardless of whether the trials are switch trials or repetition trials.	The covariate of TOT is significant in the Mixed Multilevel Logistic Regression (lower accuracy over time)
	Following a switch of the task, reaction time on said trial is higher than the average reaction time on trials of the same task where previously no switch occurred	The interaction effect between trial-type (switch vs repeat) and TOT is significant in the Mixed Multilevel Regression (higher RT for switches as TOT increases)
	Following a switch of the task, accuracy on said trial is lower than the average accuracy on trials of the same task where previously no switch occurred.	The interaction effect between trial-type (switch vs repeat) and TOT is significant in the Mixed Multilevel Logistic Regression (lower accuracy for switches as TOT increases)

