## 17. Exploratory analysis (optional)

We expect that responses on subjective questionnaires as well as demographics may be valuable covariates partially explaining the variations in reaction time and accuracy, within an exploratory analysis we, therefore, aim to investigate such possible links.

A frequently reported effect during behavioral tasks is the so-called rebound effect, of a lower performance following an error. This may also be analyzed in the context of explaining task-switching costs.

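### Time on task also counts practice, so H2.4 supports a time-on-task conclusion but not the mental-fatigue label, and the scheduled KSS and SPS ratings are not used to check it

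*Protocol article*

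**What the plan says.** Section 12 gives TOT its role: it "will be incorporated into the analysis as a key covariate indicator of mental fatigue". The Analysis Plan (under section 13) defines it for the reaction-time (RT) model as "Time on Task (Time since task onset) will be included as a" covariate, and for the accuracy model as "Time on Task (Time since task onset, and or trial number) will be included as a" covariate.

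Section 2 puts three hypotheses under the heading Mental Fatigue. The first reads "As time on task increases, the reaction times will increase regardless of whether the trials are switch trials or repetition trials"; the second concerns errors and the third switch costs, both also as functions of TOT. Table 1 sets the criteria. For the first it is "The covariate of TOT is significant in the Mixed Multilevel Regression (higher RT over time"). The second has the matching logistic criterion, and the third is judged by the TOT by trial-type interaction in both models.

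Section 10 describes at least five training blocks of 96 trials, a 96-trial refresher in session 2, and then five test blocks of 336 trials with 28-second breaks. Extra training is optional. It may be given if the last block "still shows a significant improvement over the preceding trial", and only if the participant agrees.

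KSS and SPS are completed just before the session-2 task. Afterwards, "Upon completion of the task participants will again fill in the KSS and SPS scale". Section 13 presents the SPS as the study's fatigue measure, yet neither scale appears in the two models or in Table 1. Section 17 mentions only that "responses on subjective questionnaires as well as demographics may be valuable covariates".

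**The concern.** TOT, whether as elapsed time or as trial number, rises with fatigue and with practice alike. Practice would be expected to speed responses, reduce errors and perhaps shrink switch costs; fatigue is hypothesised to do the opposite. Every participant follows the same course, section 5 describes no rested or long-break comparison, and neither model has a practice term. The TOT coefficient is therefore the net of the two processes.

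The abstract says that breaks are limited in order to induce mental fatigue. Whether fatigue was in fact induced is an empirical question, and the study schedules ratings that bear on it. As planned, those ratings have no part in the confirmatory conclusion.

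What is at stake is the interpretation of one hypothesis family. A positive slope would be labelled fatigue without evidence that fatigue rose. A flat or negative slope would be uninformative about fatigue, because practice could have hidden it. The switch-cost, similarity and conflict hypotheses are not affected.

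**Working it through.** The protocol states no figure on this point that could be reproduced. The check counts the exposure it describes and then shows, under declared assumptions, how netting works.

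**1. Exposure (section 10)**
- Minimum before the test: 5 × 96 + (48 + 48) = 480 + 96 = 576 trials.
- Test: 5 × 336 = 1,680 trials, and 1,680 / 576 = 2.9 times the minimum preparation.
- Duration at 3.5 min per 96 trials: 1,680 × 3.5 / 96 = 61 min, or about 63 min with four 28-second breaks (4 × 28 / 60 = 1.9 min).

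**2. Does the minimum training exhaust learning?** Assume that the learnable part of RT falls as N^(−c), with N the cumulative trial count. The gain from trial 576 to trial 2,256 (576 + 1,680), relative to the gain from trial 96 to trial 576, is

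(576^(−c) − 2256^(−c)) / (96^(−c) − 576^(−c)).

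| c (assumed) | Share |
|---|---|
| 0.2 | 55% |
| 0.4 | 40% |
| 0.6 | 29% |

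Under such curves the minimum training does not bring a plateau. The exponents and the curve are assumptions.

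**3. Can the extra-training criterion show a plateau?** Assume a within-person trial SD of 300 to 400 ms and a two-sided 5% comparison of two 96-trial blocks. The SE of the difference is SD × √(2/96) = 43 to 58 ms, so an observed gain must reach 1.96 × SE = 85 to 113 ms to be significant. A true gain of 40 ms would be detected 11 to 15% of the time. A non-significant last gain is therefore weak evidence that learning has stopped, and even a significant one leads to more training only at discretion and with consent.

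**4. Netting.** Net TOT change = fatigue slowing − practice gain. With 50 ms of slowing and 0, 25, 50 or 100 ms of gain, the net is +50, +25, 0 or −50 ms.

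**5. Effect on the test of the RT main effect (illustrative).** Take n = 30 (section 11), independent trial errors with SD 300 to 400 ms, and a between-person SD of the whole-session slope of 60 ms. Then

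SE = √(SD² × 12 / 1,680 + 60²) / √30 = 11.9 to 12.6 ms.

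For a two-sided 5% t test with 29 df, 60 ms of slowing alone has over 99% power. If 40 ms of practice leaves a net 20 ms, power is 34 to 37%. If practice cancels the slowing, the rejection rate is 5%. The 34 to 37% depends heavily on the assumed slope SD: it becomes 65 to 77% at 30 ms and 17 to 18% at 100 ms.

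**6. The interaction.** Practice that speeds switch and repeat trials equally cancels out of the TOT by trial-type interaction. Practice that shrinks the switch cost itself does not, and it works against H2.4.3. The document gives nothing from which to size this.

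**The case against.** The strongest defence is that H2.4.1 to H2.4.3 are worded in terms of time on task, so the planned tests answer them literally. That stands. A reader might infer that the H2.4 tests are invalid, or that the whole family rests on one covariate. The document supports neither: the tests address the stated hypotheses, and Table 1 also specifies interactions, which are protected from practice that is equal across trial types.

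Second, the protocol does mitigate practice. It trains to an adequate skill level over at least five blocks and adds a refresher, so 576 trials is a floor. A reader might take the extra-block sentence as a stopping rule, but section 10 states none. The mitigation is real; it reduces the problem without guaranteeing a plateau.

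Third, practice works against H2.4, so a positive slope is unlikely to be an artefact of practice. That also stands. The larger risk is a diluted, null or reversed effect. No passage says that a flat slope would be read as absence of fatigue; the point is that nothing in the plan guards against that reading.

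Fourth, the scales are imperfect. KSS measures sleepiness, section 13 says that the French SPS is not psychometrically validated, and two ratings in the test session cannot replace a trial-level covariate. A rise in the scales would show that fatigue or sleepiness increased, but would not separate it from practice in the slope. A quadratic term or block coding would not separate them either. These limits are accepted and shape the fix.

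Fifth, the functional form of a covariate and the handling of secondary scales are often left to a fuller analysis plan. Here, however, the article itself assigns TOT its role as fatigue indicator and the questionnaires their exploratory one.

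**Conclusion.** The point holds as a limit on interpretation. TOT mixes fatigue with practice, the training described reduces that mixing without ruling it out, and the mental-fatigue label on the TOT main effect and the TOT by trial-type interaction is not supported by the planned analysis. A null or negative slope could not be taken as evidence against fatigue.

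This rests on the structure of the design: one course for all participants, no rested comparison described, no practice term, and TOT defined as elapsed time and/or trial number. It does not rest on the illustrative power or learning figures, all of which use assumed inputs. It is worth correcting because the correction is cheap and changes what the study can say about fatigue.

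**What to change.** 1. **Manipulation check.** Pre-specify the session-2 change in KSS and SPS from before to after the task, each by a paired test. State in advance which scale decides, and note that the French SPS is not psychometrically validated.
2. **Labelling rule.** Report all H2.4 results as time-on-task effects. Call them mental-fatigue effects only if the check is met. State that a null or negative TOT slope will not be read as absence of fatigue.
3. **Form of TOT.** Enter TOT as five blocks or with a linear and a quadratic term, in the main effect and in the interaction with trial type, so that an early gain and a late slowing are both visible. State that this describes the shape and does not fully separate practice from fatigue.

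Cost: plan wording and a few extra model terms. The ratings are already scheduled, so participants carry no added burden. The downside is that the fatigue label can fail its check, leaving a conclusion about time on task only.

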## 13. Measured variables (required)

**Accuracy:** The number of correct answers during the task will be recorded.

**Reaction Time:** The reaction time on each trial will be recorded. Reaction time here is measured as the time from stimulus presentation to response (keystroke).

**Subjective Questionnaire Data:** The data from several subjective questionnaires will be recorded.

Note: All questionnaires will be presented to the participants in a paperless digitalized form.

Demographics Questionnaire:

The demographics questionnaire will include questions assessing age, gender and occupation. This questionnaire can be found in Appendix 5 in S1 Appendix.

Edinburgh Handedness Inventory:

The shortened version of the Edinburgh Handedness Inventory encompasses 4 items (e.g. writing) scored on a 5-point scale ranging from:” Always right; Usually right; Both equally; Usually left; Always left”. This shortened version has been shown to be a faster measure while maintaining its reliability [38]. A copy of the inventory is attached as Appendix 8 in S1 Appendix.

